### The interventions

#### Coaching arm

Women in the coaching arm will be enrolled in a full coaching program comprising of up to 10 calls by university qualified coaches (8 during pregnancy and 2 after birth). Health coaches, using behaviour change informed coaching techniques, will in their first call confirm and discuss the woman’s weight range target according to the IOM guidelines, and develop personally relevant lifestyle change goals and actions for participants to achieve their target weight range. In subsequent coaching calls health coaches will ensure that no conditions have presented in the pregnancy that may require medical clearance or adapted advice, revisit goals and revise them accordingly with the participant, help maintain motivation, discuss strategies for overcoming barriers and prevent relapse of healthy behaviours. Health coaches are guided by a range of national and international guidelines for nutrition, exercise and weight-gain targets for pregnancy. The timing of calls is designed to be flexible based on participant preferences and will generally last between 15 and 25 min. A recommended schedule for the pregnancy coaching calls will be used; three in the first 3 weeks, followed by a call every 2–4 weeks until the end of the pregnancy with two calls post birth.

In addition, participants in the health coaching group will be provided with supportive materials including pregnancy specific factsheets on healthy eating, exercise and the benefits of healthy weight-gain during pregnancy and a general information booklet and diary for setting and tracking health goals. Women will receive usual care from their maternity clinicians during the trial with the exception to setting their weight-gain range target and general advice about gestational weight gain at their first antenatal visit with their midwife.

#### Information only arm

Women in the information only arm will receive a one off information and coaching session from a health coach and will receive the information materials described above (with exception of the diary). Women will receive usual care from their maternity clinicians during the trial with the exception of setting their weight-gain range target and general advice about gestational weight gain at their first antenatal visit with their midwife.

### Data collection

#### Quantitative

Data for the study will be collected at baseline (prior to 18 weeks gestation), 36 weeks gestation and 12 months post-birth. Baseline, endpoint and follow up data will be self-reported by the women. These data will include validated dietary [35–37] and physical activity [38, 39] measures. Baseline and endpoint data for the coaching arm will be collected by the health coach for the coaching arm and by a research assistant for the information only arm. Coaching participants who discontinue the coaching program without withdrawing from the study will be contacted by the research assistant for their endpoint data collection. The 12 months post birth data will be collected by the research assistant.

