### Sample size

A total of 710 women will be recruited; 177 and 532 pregnant women with a pre-pregnancy BMI of 18.5–24.9 kg/m^2^ (healthy range) and ≥25.0 kg/m^2^ (overweight or obese range) respectively. 248 women will be recruited across the three rural hospitals with 462 recruited at metropolitan hospitals. The higher numbers in metropolitan hospitals is to reflect the larger target population in these areas.

The sample size has been calculated using previous reports of weight gain during pregnancy [10, 13, 33] to detect a difference of 3 kgs in gestational weight gain between intervention and control groups at 80 % power. Attrition rates of 60 % in the coaching arm and 30 % in the information only arm are expected. These rates account for the up to 15 % of women, across both arms, who start the study and go on to develop conditions during pregnancy that exclude them from further participation [34] and, allows for the perception of participant burden in the coaching arm. The relatively high attrition rate is conservative compared with other population based programs.

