### Data analysis

#### Primary objectives

All quantitative data analysis will be based on intention to treat principles. Differences between the two study groups in self-reported weight change from pre-pregnancy weight to weight at 36 weeks gestation and 12 months post birth will be tested using the independent samples *t*-test. The proportions of pregnant women who achieve weight gain within the recommended range and those who return to their pre-pregnancy weight 12 months post birth will be analysed using the *X*^2^ test. The adjusted means of the BMI outcomes at 36 weeks gestation and follow up by BMI category will be compared with the pre pregnancy BMI.

Interview data will be analysed using the thematic analysis approach. The transcribed interviews will be coded by the researchers and if there is a disagreement in the classification of interview responses, the researchers will convene as a group to discuss the discrepancies and revise coding categories if needed. Once agreement is reached, themes and sub-themes will be extracted from the data. Data from the interviews will inform the provision of recommendations for program improvement.

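### The 36-week self-reported data are collected by coaching staff in one arm and by a research assistant in the other, so the collector is confounded with arm

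*Protocol article*

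**What the plan says.** All references are to the protocol article.

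- **Mode of measurement** (Data collection, Quantitative): "Baseline, endpoint and follow up data will be self-reported by the women".
- **Collector at baseline and 36 weeks** (same section): "Baseline and endpoint data for the coaching arm will be collected by the health coach for the coaching arm and by a research assistant". The sentence goes on to assign the research assistant to the information only arm.
- **Exception within the coaching arm** (same section): "Coaching participants who discontinue the coaching program without withdrawing from the study will be contacted by the research assistant for their endpoint data collection".
- **Collector at 12 months** (same section): "The 12 months post birth data will be collected by the research assistant". No distinction by arm is made.
- **Use of the data** (Data analysis, Primary objectives): differences between arms in "self-reported weight change from pre-pregnancy weight to weight at 36 weeks gestation and 12 months post birth will be tested" with an independent-samples t-test. The proportion within the recommended range is compared with a chi-squared test. Diet scores and confidence to change are analysed under Secondary objectives.
- **The coach's role** (Coaching arm): in the first call the coach is to "confirm and discuss the woman’s weight range target according to the IOM guidelines, and develop personally relevant lifestyle change goals". Later calls return to those goals and support motivation. The target range itself is set at the first hospital visit in both arms (Study design, Coaching arm, Information only arm). Information-arm women have a single coach session.
- **Target difference** (Sample size): "to detect a difference of 3 kgs in gestational weight gain between intervention and control groups at 80 % power", with expected attrition of 60% in the coaching arm and 30% in the information only arm.

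**The concern.** What a woman says she weighs can depend on who is asking. At 36 weeks, a woman still in coaching is asked by the service that has worked with her on reaching a weight range. A woman in the information only arm is asked by someone with no part in the intervention. If the two groups report differently for that reason alone, the difference enters the comparison of arms directly.

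This would touch the mean weight change at 36 weeks. It would also touch the proportion within the recommended range, where a small shift can move women across a threshold, and the 36-week diet and confidence scores. The collector also changes with adherence inside the coaching arm, so the arm's own data are not collected in one way.

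**Working it through.** **Step 1. Can the analysis separate collector from arm?** Set the 36-week data out by arm and collector, as Data collection, Quantitative assigns them:

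| | Health coach | Research assistant |
|---|---|---|
| Coaching arm | women still in the programme | discontinuers who remain in the study |
| Information only arm | none | all |

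One cell is empty, so no information-arm woman shows what reporting to a coach does. The one within-arm contrast, coach against research assistant in the coaching arm, compares women who stayed with women who stopped. A collector effect cannot be estimated from that contrast without mixing it with adherence.

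**Step 2. How many women are coach-collected?** The article gives 710 women and 60% and 30% attrition, but no numbers per arm. Assuming equal arms, 710/2 = 355 each.

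- Coaching women remaining: 0.4 × 355 = 142
- Coaching women lost to attrition: 0.6 × 355 = 213
- Information-arm women remaining: 0.7 × 355 = 248.5

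The 710 itself cannot be reproduced from the article, which gives no standard deviation. Nothing here depends on it beyond these counts.

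**Step 3. Size of the shift, by assumption.** Let s be the extra under-reporting to a coach compared with a research assistant. The article gives no value, so take s = 0.5 to 1.5 kg. The shift in the coaching-arm mean is s × (coach-collected women / analysed coaching women). It depends on how many of the 213 are programme discontinuers whom the research assistant reaches:

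| Of the 213, reached | Analysed | Coach-collected share | Shift in arm mean | Share of 3 kg |
|---|---|---|---|---|
| none | 142 | 142/142 = 100% | 0.5 to 1.5 kg | 17 to 50% |
| half (106.5) | 248.5 | 142/248.5 = 57% | about 0.3 to 0.9 kg | 10 to 29% |
| all | 355 | 142/355 = 40% | 0.2 to 0.6 kg | 7 to 20% |

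The first row is the ceiling for the assumed range of s.

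**Step 4. What the ceiling would do to the test.** This is an illustration only. Assume no true effect, a two-sided 5% test, no clustering, and 142 against 248.5 women. With an arm-mean shift b and SE = SD × √(1/142 + 1/248.5), the false-positive rate is 1 − Φ(1.96 − b/SE) + Φ(−1.96 − b/SE). For an assumed SD of 6 kg, SE = 0.631.

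| Shift b | SD 5 kg | SD 6 kg | SD 8 kg |
|---|---|---|---|
| 0.5 kg | 16% | 12% | 9% |
| 1.0 kg | 48% | 35% | 22% |
| 1.5 kg | 81% | 66% | 43% |

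Both b and SD are assumptions. The table shows only that a shift well below 3 kg would matter to the test if it occurred.

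**The case against.** Much of the case on the other side is sound and limits the point.

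- **The coach does not set the target.** A reader might infer that women report to the person who set their goal. The article has the hospital set the range in both arms, and the coach confirms and discusses it. Nor does it say that the same individual coach takes the 36-week data; it says only the health coach. What stands is that the collector is intervention staff in one arm and not in the other.
- **Direction is not shown.** The outcome is a change from pre-pregnancy weight, and the coach also collects baseline data. If pre-pregnancy weight is taken at that contact and under-reported too, apparent gain would rise and partly offset under-reporting at 36 weeks. The article does not settle this.
- **Discontinuers dilute the shift.** Under intention to treat, those reached by the research assistant enter the coaching arm, as Step 3 shows. Dilution reduces the size but leaves collector tied to adherence.
- **Only part of primary objective (i) is exposed.** It also covers retention at 12 months, where the research assistant takes the weight.
- **The design is pragmatic and coaching women are already burdened.** This is a fair reason to avoid extra contacts. But the pragmatic argument concerns how the service is delivered, and it does not require outcome data to be collected differently by arm.

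None of this removes the difference in collector at 36 weeks, and nothing else in the article neutralises it.

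**Conclusion.** The point holds as a risk of differential reporting at 36 weeks that the planned analysis cannot separate from a treatment effect. It plausibly favours coaching, because the coach works on weight goals with the woman.

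A reader might go further and infer a demonstrated bias of known direction and size in the whole primary outcome. The article does not support that: it gives no direction or size, and the 12-month weight is collected by the research assistant. The 17 to 50% of the target difference is a ceiling. It rests on an assumed 0.5 to 1.5 kg shift and on every analysed coaching woman being coach-collected. With half of the discontinuers reached, it falls to about 10 to 29%. The counts also assume equal arms. The change is worth making because it is cheap and the problem cannot be repaired afterwards.

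**What to change.** In Data collection, Quantitative, state that the research assistant collects the 36-week data in both arms, in the same way, whether or not a woman is still in coaching. The research assistant already has this task for the information only arm and for coaching discontinuers, and collects the 12-month data, so no new role or procedure is needed.

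Costs and limits:

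- About 142 extra short calls, assuming 355 women per arm and 60% attrition.
- One extra contact for women who complete coaching, with a small risk of missed calls.
- Some goal-directed reporting may remain whoever asks, because women know they were coached. The change removes the difference in collector, not the reliance on self-report.

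Moving baseline collection as well would add up to about 355 calls and is not essential. The 36-week contact is the priority.

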#### Qualitative interviews

Semi-structured telephone interviews (Additional files 1, 2 and 3) will be conducted by three researchers experienced in qualitative data collection methods (VC, KL and JR). Interviews will be recorded using a digital recorder and transcribed by a professional transcription service. Interview guides will be used to illicit the study participants’ experiences of the service, usefulness of program resources and suggestions for service improvement. Interviews will be conducted with the following:Up to 22 pregnant women in the coaching arm. A subset of this group will include women who actively withdraw from the coaching program.Up to 18 pregnant women in the information only arm.Up to 35 healthcare professionals (including clinic managers, midwives, doctors, and health coaches) who have contributed to the program by coordinating at the hospitals, recruiting pregnant women, providing medical clearance or delivering the service.

### Data analysis

#### Primary objectives

All quantitative data analysis will be based on intention to treat principles. Differences between the two study groups in self-reported weight change from pre-pregnancy weight to weight at 36 weeks gestation and 12 months post birth will be tested using the independent samples *t*-test. The proportions of pregnant women who achieve weight gain within the recommended range and those who return to their pre-pregnancy weight 12 months post birth will be analysed using the *X*^2^ test. The adjusted means of the BMI outcomes at 36 weeks gestation and follow up by BMI category will be compared with the pre pregnancy BMI.

Interview data will be analysed using the thematic analysis approach. The transcribed interviews will be coded by the researchers and if there is a disagreement in the classification of interview responses, the researchers will convene as a group to discuss the discrepancies and revise coding categories if needed. Once agreement is reached, themes and sub-themes will be extracted from the data. Data from the interviews will inform the provision of recommendations for program improvement.

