**Methods/Design:**

This study aims to compare the effectiveness of a telephone-based health coaching program versus provision of information only in supporting pregnant women to achieve appropriate gestational weight gain. A pragmatic stratified clustered randomised controlled trial will be conducted with 710 women who present to 5 hospitals for their first antenatal appointment during the recruitment period (6–8 months), have a pre-pregnancy body mass index (BMI) ≥ 18.50 (healthy weight or above), are 18 years and over, singleton gestation, English speaking, have no pre-existing medical conditions that may limit their ability to exercise or require a restricted diet and are 18 weeks or less gestation. Hospitals will be randomised into one of two intervention models: a) information only; or b) information plus 10 telephone-based health coaching sessions with a university qualified coach. Both interventions will set a weight-range target with pregnant women. The women attending antenatal clinics at participating hospitals will be screened at their initial hospital appointment to assess their eligibility. Women recruited to the trial will have a number of measures recorded including anthropometrics (self-reported height and weight) and dietary and physical activity scores during and following pregnancy. These measurements will be collected at baseline (prior to 18 weeks gestation), 36 weeks gestation and 12 months post-birth.

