### The NSW Get Healthy in Pregnancy Service (GHiP)

A telephone-based service for pregnant women of New South Wales (NSW), Australia, Get Healthy in Pregnancy (GHiP), was developed in collaboration between the NSW Office of Preventive Health and NSW Kids and Families to support women to achieve appropriate gestational weight gain through health coaching. GHiP was developed as an enhancement to the GHS. Development of GHiP has been informed by evaluations of other interventions aimed at reducing EGWG with the input of an Expert Advisory Panel including midwives, obstetricians, dietitians and antenatal educators from across NSW. Pregnant women have suggested in a qualitative study in the UK that they would prefer a healthy eating service that is integrated into routine care and provides information early in their pregnancy [27]. Two potential models for the GHIP integrated with hospital antenatal care have been developed and will be compared as the two arms in this study:*Information only* – introduction of gestational weight gain recommendations by midwife at their initial hospital antenatal appointment, evidence-based factsheets and an information booklet on healthy eating, exercise and weight gain during pregnancy in line with Australian guidelines [28–30], and a single health coaching call; and*Health coaching* – introduction of gestational weight gain recommendations by midwife at their initial hospital antenatal appointment, the same factsheets and information booklet as the information only group, plus a journey booklet to record progress and up to 10 health coaching calls (8 during pregnancy, 2 post pregnancy).

Both service models commence between 12 and 22 weeks gestation. Participants receiving health coaching are offered coaching calls up until 36 weeks gestation and receive two coaching calls at 10 and 14 weeks post-delivery.

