### Study setting

The study will be conducted in the antenatal clinics of five NSW hospitals of which three are rural (Orange Base, Lismore Base and Dubbo Base) and two metropolitan (Liverpool and Blacktown). Hospitals were recruited through an expression of interest process addressed to the general manager of each site in the first instance. Agreement was also obtained from the midwifery unit manager and obstetric lead of the maternity unit at each hospital to ensure local support prior to inclusion. All hospitals are public hospitals accounting for approximately 10 % of the total births in NSW and the demographic characteristics of women attending the two metropolitan and the three rural hospitals are similar within their categories. The hospitals offer a variety of antenatal care options for women including hospital-based, shared care with general practitioners or via community based midwifery group practices. All of these care models require women to attend the hospital for an initial antenatal appointment which usually occurs after 12 weeks of gestation.

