### Participants

Participants will be 710 pregnant women who attend one of five hospitals during the recruitment period and are English speaking, 18 years and over, have a singleton pregnancy, have a gestation of 18 weeks or under and agree to participate (signed consent forms and verbal consent provided at first coaching call).

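### The primary comparison counts weight gain from before pregnancy and does not adjust for gain made before either service starts, by which time a third to three fifths of the 36-week window has passed.

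*Protocol article*

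**What the plan says.** Under Data analysis, Primary objectives, the protocol article compares "Differences between the two study groups in self-reported weight change from pre-pregnancy weight to weight at 36 weeks gestation". The same sentence covers weight change to the later time point and names the test: "12 months post birth will be tested using the independent samples *t*-test". No covariate is given.

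The timing of the services is set out in the section on the GHiP service: "Both service models commence between 12 and 22 weeks gestation". It also says that "Participants receiving health coaching are offered coaching calls up until 36 weeks gestation". Under Participants, women must "have a gestation of 18 weeks or under and agree to participate". Study setting explains that all care models require women to "attend the hospital for an initial antenatal appointment which usually occurs after 12 weeks of gestation".

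The Abstract lists the recorded measures as "including anthropometrics (self-reported height and weight) and dietary and physical activity scores during and following pregnancy". Data collection, Quantitative places the baseline measurement before 18 weeks. A health coach collects it in the coaching arm and a research assistant in the information only arm.

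No other stated analysis uses weight or gestation at entry:
- The adjusted BMI means under Primary objectives are set against pre-pregnancy BMI, and the adjustment variables are not named.
- The mixed model under Secondary objectives lists demographic variables, socio-economic status, age, pre-pregnancy BMI and parity.

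**The concern.** The coaching programme can only influence weight gained after it begins. The outcome also counts everything gained from conception to that point, and the named test neither removes this part nor adjusts for it.

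Two things are at stake. The first is precision: variation between women in early gain stays in the error term. The second is protection against imbalance. Five hospitals form four randomised units, because two rural hospitals are combined (Study design). Stratification by region then leaves two units per stratum. Women are recruited after their hospital has been allocated, and each hospital develops its own referral process. The Discussion accepts that recruitment may depend on local leadership, champions and the organisation of care. Early gain or gestation at entry could therefore differ between hospitals, and so between arms. An unadjusted t-test would report such a difference as part of the coaching effect.

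**Working it through.** **Inputs from the protocol article.** Outcome window: pre-pregnancy to 36 weeks (Primary objectives). Service start: 12 to 22 weeks (GHiP section). Entry limit: 18 weeks (Participants). Target difference: 3 kg at 80% power, total 710, expected attrition 60% and 30% (Sample size). The article gives no weight-accrual curve, no SD and no correlation between early and total gain.

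**The plan's own figure.** The total of 710 cannot be reproduced forwards, because no SD, alpha or design effect is stated. It can be solved backwards, assuming two-sided alpha 0.05, 355 women per arm and no design effect. Completers are 355 × 0.4 = 142 and 355 × 0.7 = 248.5. The implied SD is 3 / [(1.960 + 0.842) × √(1/142 + 1/248.5)] = about 10.2 kg. The point below does not depend on this value.

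**Step 1: share of the window in weeks.** Start week / 36 gives 12/36 = 33%, 18/36 = 50% and 22/36 = 61%.

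**Step 2: share in kilograms.** Assume weekly gain in weeks 0 to 12 is r times the later weekly rate. The share accrued by start week s (12 or later) is (12r + s − 12) / (12r + 24).

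| r (assumed) | start 12 | start 18 | start 22 |
|---|---|---|---|
| 0 | 0% | 25% | 42% |
| 0.25 | 11% | 33% | 48% |
| 0.5 | 20% | 40% | 53% |
| 1 | 33% | 50% | 61% |

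Over this range, the share of weight equals the share of weeks only at r = 1, which is linear gain from conception.

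**Step 3: weeks left for the calls to act.** 36 − 12 = 24 weeks and 36 − 22 = 14 weeks. A 3 kg difference spread over the whole window is 3/36 = 0.083 kg/week. Produced only after service start, it needs 3/24 = 0.125 to 3/14 = 0.214 kg/week. At a constant 0.125 kg/week (assumed), the difference reached is 24 × 0.125 = 3.0 kg for a start at 12 weeks and 14 × 0.125 = 1.75 kg for a start at 22.

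**Step 4: precision from adjustment.** If early gain correlates ρ with total gain within arm, the residual SD is multiplied by √(1 − ρ²). At ρ = 0.3 this is √0.91 = 0.95, and at ρ = 0.6 it is √0.64 = 0.80, a reduction of about 5% to 20%. Both values of ρ are assumed, and clustering is ignored.

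**Step 5: imbalance.** An arm difference of 0.5 kg in pre-service gain (assumed) enters the unadjusted difference in total gain kilogram for kilogram. Relative to the target it is 0.5/3 = 17%.

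**The case against.** The outcome suits the question. The IOM ranges are tied to pre-pregnancy BMI, the target set at booking follows them, and excess gain is defined by them. Gain from pre-pregnancy is the matching continuous measure. This stands, so the outcome should be kept.

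A reader might infer that the comparison is biased. The documents do not support that. Under randomisation, gain that the calls cannot affect is noise, with no bias in expectation. Bias in the realised result needs a chance or recruitment difference between hospitals. With so few units that risk applies to every prognostic factor, but here the relevant covariate appears to be collected already.

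Start time and exposure length are part of the pragmatic service being tested. A smaller effect with later starts would be the real-world effect, so Step 3 shows no error in the estimate. This also stands. What remains is that start time could differ by hospital for reasons unrelated to coaching.

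Covariates are often left to an analysis plan, and none is shown here. One may well add this adjustment. The article nevertheless commits to a specific test without it.

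The remedy has limits too. Baseline falls before 18 weeks while services may start up to 22, so some pre-service gain is missed in later starters. The collector of baseline data differs by arm, and no text places the coaching-arm baseline before the first call. That current weight is recorded separately from pre-pregnancy weight is a reasonable inference, but the article does not say so. These points shape the fix without defeating it.

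**Conclusion.** The point holds as a weakness in the chosen analysis that should be corrected. The outcome definition is sound. Between 33% and 61% of the 36-week window has passed before either service starts, and the named test makes no allowance for gain in that period.

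It would be wrong to read this as a third to three fifths of the weight gain. The documents give no accrual curve. With r between 0 and 1, the share of weight is 0% to 33% for a start at 12 weeks and 42% to 61% for a start at 22. The issue may be negligible for the earliest starters but is material for the latest under every value of r tried.

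The 5% to 20% reduction in residual SD and the 17% from a 0.5 kg imbalance are illustrations resting on assumed inputs. The structural facts (the window, the start times, the unadjusted test and the four units) come from the article.

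**What to change.** Under Data analysis, Primary objectives:

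- Keep gain from pre-pregnancy to 36 weeks as the outcome, and leave the IOM-range classification as it is.
- Replace the t-test for this outcome with a regression on arm, adjusted for gain already made at baseline (baseline minus pre-pregnancy self-reported weight) and gestational age at baseline.
- Report gain from baseline to 36 weeks as a supporting result without the early-gain covariate. With both covariates included, it would give the same arm estimate as the main model.

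Under Data collection, state that current weight at baseline is recorded separately from pre-pregnancy weight. State also that, in both arms, the value used is the one reported at the start of the first contact, before any coaching.

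**Cost.** This is mostly wording, but fixing when the baseline weight is taken may need a small change to the collection procedure. Women without a baseline weight need a pre-stated imputation rule. Some pre-service gain in women who start after baseline stays unadjusted. Any difference in reporting to a coach versus a research assistant could enter through the covariate, which is why the weight must precede coaching. The adjustment does not address clustering by hospital, which needs its own treatment.
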